### Statistical analysis

The “intension to treat” analysis will be applied in this study. The descriptive analysis of all measurement data is implemented using mean, standard deviation, median, interquartile range, maximum and minimum indicators; the descriptive analysis of count data is implemented using index such as rate, ratio and RR. The primary analysis will be a simple categorical frequency comparison for unfavorable outcome by means of Chi-square test, so will the categorical data of secondary outcomes. The continuous outcomes will be analyzed by t-test. The log-rank method will be used in the analysis of time- to-event type of outcomes. Subgroup analysis stratified by age, location of hematoma, volume of hematoma, GCS at hospitalization, with/without intraventricular hemorrhage, and midline shift is preplanned. Statistical inference is conducted using the above-mentioned hypothesis testing method and confidence interval may also be used when necessary. P values ≤0.05 (α = 0.05) will be considered statistically significant. All statistical analysis is performed using SAS or SPSS statistical software.

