### Sample size

It was reported that the rate of poor outcome of patients with a hemorrhage volume above 30 ml who received craniotomy is about 49% to 67% [19,21,24]. Previous studies showed that the MIS could decrease the rate of poor outcome by about 7% to 22% [19,21] compared with craniotomy. We assume that the neuroendoscopy and stereotactic aspiration can reduce the rate of poor outcome from 58% to 51%, and a sample size of 2203 patients will be required with a significance level of 5% (2-sided) and a power of 80%. In consideration of ensuring the quality of research, the sample size is enlarged to 2448 (816 In each arm).

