### Randomization

Patients will be allocated to neuroendoscopy group, stereotactic aspiration group and craniotomy group by method of simple randomization. The randomized number was created before the trial by SPSS 19.0 and kept in envelopes. The envelopes within randomized number will be sent to the centers before trial begin.

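### The primary chi-square is valid and adequately powered for the global test, but it leaves unused the prognostic baseline factors the plan already names; a prespecified adjusted analysis would gain power with no extra patients

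*Protocol article*

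**What the plan says.** The Statistical analysis section fixes the primary test: "The primary analysis will be a simple categorical frequency comparison for unfavorable outcome by means of Chi-square test". It mentions no covariate-adjusted analysis. The same section names six baseline factors, but for another purpose: "Subgroup analysis stratified by age, location of hematoma, volume of hematoma, GCS at hospitalization, with/without intraventricular hemorrhage, and midline shift is preplanned".

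Under Randomization, patients are allocated "by method of simple randomization". No stratification factor is given, neither severity nor centre, although 20 centres take part.

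The Sample size section assumes 58% poor outcome with craniotomy and 51% with each of the other two techniques. It then says that "a sample size of 2203 patients will be required with a significance level of 5% (2-sided) and a power of 80" per cent, and adds: "In consideration of ensuring the quality of research, the sample size is enlarged to 2448", which is 816 per arm. No loss rate is stated.

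Table 1 lists GCS, NIHSS and imaging at baseline. The CT scan section schedules a scan at admission and describes how hematoma volume is calculated.

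**The concern.** The plan treats six baseline factors as important enough to define subgroups, yet uses none of them in the primary comparison. Simple randomization does not balance them by design either. Where such factors predict death or dependency, an unadjusted comparison counts explainable variation between patients as noise. A prespecified adjusted analysis of the same patients would then have more power.

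This matters most for the comparison of each minimally invasive technique with craniotomy, where the margin is thinner than for the global test. It also matters for credibility. If simple randomization happens to leave a visible difference in GCS or volume, an adjustment added afterwards would look data-driven, whereas one fixed now would not.

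**Working it through.** **Inputs from the Sample size section.** Rates 58%, 51%, 51%; two-sided 5%; 80% power; 2203 required; 2448 planned (816 per arm).

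**Step 1: reproduce the plan's figure.** Take the three-group chi-square with 2 degrees of freedom.
- Mean rate = (0.58 + 0.51 + 0.51)/3 = 0.5333.
- Effect per patient in each arm: w = Σ(p − mean)² / [mean × (1 − mean)] = 0.003267/0.248889 = 0.013125.
- Noncentrality for 80% power at 5% with 2 df: 9.635.
- n per arm = 9.635/0.013125 = 734.07, so N = 2202.2, rounded up to **2203**. This matches the plan exactly.
- 2203/0.90 = 2447.8, rounded up to **2448**. An allowance of about 10% loss therefore fits, but it is inferred.

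Other readings do not give 2203. For example, pairwise two-sided 5% gives 794 per arm (2382 for three arms), and the two minimally invasive arms pooled against craniotomy give 1788.

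**Step 2: power of the test as planned.**
- Global 2-df test: 80.0% at 2203; 84.3% at 2448 (noncentrality 816 × 0.013125 = 10.71).
- Pairwise 58% vs 51% at two-sided 5%, no multiplicity correction: z = [0.07√n − 1.96√(2 × 0.545 × 0.455)] / √(0.58 × 0.42 + 0.51 × 0.49). At n = 816, z = 0.88 and power is 81.1%. At n = 734, z = 0.735 and power is 76.9%.

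**Step 3: effect of adjustment.** The documents give no prognostic strength. Let R² be the share of outcome variance explained by the baseline covariates (assumed). Adjustment then acts approximately as if n were n/(1 − R²).

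| R² (assumed) | Global, 816/arm | Global, 734/arm | Pairwise, 816/arm | Pairwise, 734/arm | N for 80%, global |
|---|---|---|---|---|---|
| 0 (as planned) | 84.3% | 80.0% | 81.1% | 76.9% | 2203 |
| 0.05 | 86.2% | 82.1% | 83.0% | 79.0% | 2093 |
| 0.10 | 88.0% | 84.3% | 85.0% | 81.1% | 1982 |
| 0.20 | 91.6% | 88.4% | 88.8% | 85.4% | 1762 |
| 0.30 | 94.8% | 92.4% | 92.5% | 89.7% | 1542 |

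**Step 4: check by simulation.** Logistic regression with a 2-df Wald test, 816 per arm, 3000 replicates per setting, one normal baseline predictor. Unadjusted to adjusted power was 84.9% to 88.2% (R² 0.075), 84.1% to 90.7% (0.17) and 84.6% to 95.4% (0.29). Simulated type I error lay between 4.4% and 5.6% across both tests. The approximation in step 3 is adequate, and both tests hold their level.

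**The case against.** The strongest reply is that nothing here is wrong. The chi-square is valid under simple randomization, it is the test the sample size was built on, and it reaches the planned power. That stands, and it limits the point to efficiency.

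Three stronger readings are tempting, and the documents do not support them.

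- *The trial is underpowered.* The stated 80% belongs to the global test, which meets it. Pairwise power is 81.1% at 816 per arm. It falls to about 77% only under a loss of about 10%, which the plan never states. Whether the trial should have been sized for pairwise contrasts is a separate question.
- *Chance imbalance biases the result.* Over repeated randomizations the unadjusted risk difference is unbiased, and chance imbalance is part of the variance the test already allows for. With 816 per arm, the standard error of a standardised baseline difference between two arms is √(2/816), about 0.05.
- *Adjustment is certain to restore 80% pairwise power at no cost.* At R² 0.05, pairwise power at 734 per arm reaches only 79.0%. The entry criteria also narrow the prognostic range: GCS is limited to 5 to 12, volume has a 30 ml floor, and severe intraventricular hemorrhage, terminal herniation and prior disability are excluded. A high R² therefore cannot be taken for granted. The simulation used a single, correctly specified predictor and no missing values, which favours adjustment.

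Two further objections stand in part. An adjusted odds ratio is a different quantity from the risk comparison the trial was sized on; standardised risk differences answer this for the estimate, although a test of model coefficients does not correspond to them exactly. An adjusted supportive analysis may also exist in an analysis plan that is not shown. That would not change the primary test, which the article itself fixes.

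**Conclusion.** The point holds as an efficiency recommendation. The plan fixes an unadjusted primary test while naming the prognostic factors that could sharpen it.

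For assumed R² between 0.05 and 0.30, the gain in global power at 816 per arm is about 2 to 10 percentage points. In pairwise power at 734 per arm it is about 2 points at R² 0.05, 4 at 0.10 and 8 to 9 at 0.20. The direction is secure if the covariates are prognostic; the size rests wholly on the assumed R². The pairwise figures also assume about 10% loss and no multiplicity correction.

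That intraventricular hemorrhage and midline shift are recorded at baseline is inferred from baseline imaging and from the subgroup plan, which cannot be carried out without them.

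**What to change.** In the Statistical analysis section and the analysis plan:

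- Make the primary analysis a logistic regression of unfavorable outcome on arm, adjusted for a short fixed list: age, baseline GCS and hematoma volume as continuous terms, plus location, intraventricular hemorrhage and midline shift.
- Use a global 2-df test of arm as the primary test.
- Report standardised (marginal) risk differences against craniotomy with confidence intervals, so that the result can be read on the 58%-to-51% scale.
- Keep the unadjusted chi-square as a named sensitivity analysis.
- Fix the functional form of each covariate, the handling of missing baseline values and the use or omission of a centre term for the 20 sites before anyone sees unblinded outcomes.

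The cost is a change to the published primary analysis and the prespecification work just listed. No extra patients are needed and, if the subgroup factors are recorded as the plan implies, no extra data. If the sponsor prefers to leave the chi-square as primary, the adjusted model should at least be prespecified as the key sensitivity analysis; the primary test would then forgo the gain in power.

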## Background

Spontaneous intracerebral hemorrhage (sICH) is the most devastate kind of all stokes. It was estimated that sICH affects over 1 million people worldwide every year [1,2]. The case fatality rate of sICH at 30 days is about 30%-55%, and only 12%-39% of the survivors could live independently after 6 months [3-5].

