#### Secondary outcomes

The secondary outcomes include: mortality at 30 days, and 6 months after surgery; neurological functional status of 6 months after surgery measured by GOS, Modified Rankin Scale (mRS), Barthe index (BI), and National Institutes of Health Stroke Scale (NIHSS) separately; complications include rebleeding, ischemic stroke, intracranial infection; days of hospitalization.

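### A two-sample t-test is fixed for continuous secondary outcomes in a three-arm trial with no contrasts named, and for hospital days it lets early death count as a short stay

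*Protocol article*

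**What the plan says.** The Statistical analysis section of the protocol article states an intention-to-treat analysis. It assigns a chi-square test to the primary outcome, adds "so will the categorical data of secondary outcomes", and then says without qualification: "The continuous outcomes will be analyzed by t-test". A log-rank method is reserved for time-to-event outcomes, which are not named. The significance threshold is P ≤ 0.05.

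The Sample size section sets three equal arms: "the sample size is enlarged to 2448 (816 In each arm").

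The Secondary outcomes section lists "neurological functional status of 6 months after surgery measured by GOS, Modified Rankin Scale (mRS), Barthe index (BI), and National Institutes of Health Stroke Scale", and later "complications include rebleeding, ischemic stroke, intracranial infection; days of hospitalization". It does not say which of these are continuous. Days of hospitalization plainly is, and BI and NIHSS are naturally read so.

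On mortality, the Background says "The case fatality rate of sICH at 30 days is about 30%-55" per cent. That describes the disease in general. No mortality is assumed for any trial arm.

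**The concern.** A t-test compares two groups and the trial has three. The plan does not say whether each minimally invasive arm is compared with craniotomy, the two are pooled, or all three pairs are tested.

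The mean is also a poor summary where many patients die early. A hospital stay stops at death, so a comparison of mean stay credits an arm for losing patients soon after surgery. For BI and NIHSS, a patient who has died has no observed 6-month value, so a mean needs a decision about the dead before it can be computed.

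The Study objective section makes the separate effects on death and dependency, and the days of hospitalization, an aim of the trial. An arm that saves lives could be reported as worse on stay, and possibly on function.

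**Working it through.** **1. Which test does the sizing fit?**

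Inputs from Sample size: 58% v 51% v 51%, two-sided 5%, power 80%, total 2203.

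- Mean proportion = (0.58 + 0.51 + 0.51)/3 = 0.5333.
- Mean squared deviation = (0.04667² + 2 × 0.02333²)/3 = 0.001089.
- w² = 0.001089/(0.5333 × 0.4667) = 0.004375.
- Noncentrality for 80% power on 2 df = 9.635.
- N = 9.635/0.004375 = 2202.2, rounded up to 2203.

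The plan's figure is reproduced by a three-group chi-square. A pairwise two-sided calculation gives 794 per arm, or 2382 in all, which does not match. So the sizing fits a three-group test, while continuous outcomes are given a two-group one. If all three pairs were t-tested at 0.05 without adjustment, the family-wise error would be 12.2% (studentized range, three groups).

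**2. Hospital days.**

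The documents give no stay lengths and no arm mortality, so these are assumptions: survivors' mean stay S, decedents' mean stay D, mortality m of 30% v 37%, and identical S and D in both arms.

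- Mean stay = (1 − m)S + mD, so the difference between arms = 0.07 × (S − D).
- Variance per arm = (1 − m)·SD_S² + m·SD_D² + m(1 − m)(S − D)².
- SE = √[(V₁ + V₂)/816]. Chance of significance in that direction = Φ(difference/SE − 1.96).

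| S, D (days) | SD survivors, deaths | Shift (days) | SE | z | Chance of P < 0.05 |
|---|---|---|---|---|---|
| 14, 5 | 10, 3 | 0.63 | 0.46 | 1.36 | 27% |
| 21, 7 | 10, 3 | 0.98 | 0.53 | 1.86 | 46% |
| 22, 7 | 12, 4 | 1.05 | 0.61 | 1.73 | 41% |
| 21, 5 | 10, 3 | 1.12 | 0.56 | 2.01 | 52% |

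The extreme corners of the same ranges give 0.07 × (14 − 7) = 0.49 and 0.07 × (22 − 5) = 1.19 days. Moving mortality to 20% v 27% or 40% v 47% leaves each shift unchanged. With SDs of 10 and 3, the chance of significance over the three mortality levels runs from 26% to 53%. In every row the arm with more deaths has the shorter mean stay.

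**3. BI, if it is treated as continuous.**

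Assumptions: existing survivors have mean BI 65 (SD 30). One arm saves a further 7% of patients, whose BI averages 10, 20 or 30 (SD 15). Mortality in the other arm is m₀ = 20%, 30% or 40%.

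- Survivor-only mean in the life-saving arm = [(1 − m₀) × 65 + 0.07 × b]/(1 − m₀ + 0.07). With m₀ = 0.30 and b = 20: (45.5 + 1.4)/0.77 = 60.9, which is 4.1 points lower than 65.
- With death scored 0: 46.9 − 45.5 = 1.4 points higher. In general, with death scored d, the difference is 0.07 × (b − d).

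Over the grid, the survivor-only comparison puts the life-saving arm 2.8 to 5.7 points lower (z −1.7 to −2.9). Scoring death as 0 puts it 0.7 to 2.1 points higher. The sign depends on how death is handled.

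**The case against.** **Two-group contrasts may be intended.** The abstract frames the question as minimally invasive surgery against craniotomy, and a t-test is usable for a two-group contrast. That stands as far as it goes. The gap is that no pairs and no multiplicity rule are named, while the Study objective section treats all three techniques alike.

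**Survivors only.** A reader might infer that BI and NIHSS will be compared among survivors. The article does not say so. It does not class these scores as continuous, it states intention to treat, and it does not exclude a worst-score rule, which may sit in the full protocol or SAP. Their silence here is no fault, so this part of the point is conditional.

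**A count of patients lost.** A reader might apply the 30%-55% fatality to 816 and conclude that 245 to 449 patients per arm have no score. The documents do not support that as a trial rate. The figure covers the disease in general, and 55% exceeds the 51% assumed for death and dependency together in two of the three arms (the article assumes treatment "can reduce the rate of poor outcome from 58% to 51" per cent). That would be 449 deaths against 0.51 × 816 = 416 poor outcomes of any kind.

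**mRS and GOS.** A chi-square on these scales is valid for three groups, and the article does not say whether they will be grouped. An ordinal model would be more efficient, but that is a preference and not an error.

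**Size.** The stay example rests wholly on assumed inputs, and three of its four rows have z below 1.96. Mortality at 30 days and 6 months is also a secondary outcome, so a misleading stay would be read beside it. Both objections stand and limit the weight of the point.

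**Conclusion.** The point holds for what the article fixes: a two-sample t-test for continuous outcomes in three arms with no named contrasts, applied to a hospital stay that death shortens. The direction of the distortion needs only that patients who die have shorter stays than survivors. Its size, about 0.6 to 1.1 days for a 7-point mortality difference, depends on the assumed stays. It is large enough to reach significance in roughly a quarter to a half of trials of this size under the combinations tabulated.

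For BI and NIHSS the point holds only if they are analysed as continuous. A mean then either leaves out the dead, contrary to intention to treat, or turns on an arbitrary number. The point is worth correcting but moderate in weight: only secondary outcomes are touched, and the primary outcome already counts death.

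**What to change.** Replace the t-test by a Kruskal-Wallis test across the three arms for BI, NIHSS and hospital stay. Follow it with pairwise Wilcoxon tests only if it is significant. Rank death worst for all three outcomes, and state for hospital stay which deaths this covers. An alternative to ranked stay is days alive and out of the index admission to day 30. Extending that measure to 6 months, or counting all hospital days, would need readmission data, which Table 1 does not list. Show survivor-only scores and stay descriptively, with mortality beside them. An ordinal analysis of mRS and GOS, where death is already a category, is optional.

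The cost is wording. The scores are scheduled in Table 1, stay and mortality are already outcomes, and deaths are recorded as serious adverse events. The small downside is that a rank-based effect is less familiar to readers than a mean difference.

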### Data collection and follow-up

After patient enrollment, we will collect their basic data at neurological evaluation, functional status assessment and imaging for baseline information, and follow up data will be collected at the time of seven days, one month, three months and six months after surgery. The plan of data collection is showed in Table 1. All the data will be recorded in the CRF in time. The filled CRF will be sent to trial secretary expeditiously.

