## Discussion

SICH has always been a frequently discussed topic in neurology and neurosurgery. Though there are over 10 randomized studies aimed to find the best treatment for patients with sICH, it is still very difficult to select individualized treatment for each patient. MISTICH is the first large-scale randomized, parallel-group clinical trial to provide robust evidence for clinical practice by assessing the safety and efficacy of different minimally invasive surgical methods for sICH. A total of 2448 patients will be enrolled in this study. The primary outcome is unfavorable outcome at 6 months. The complications and trends towards improved neurological outcome will also be investigated in this study.

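### The t-test fixed for continuous outcomes leaves baseline NIHSS out of the 6-month NIHSS comparison, which costs precision but causes no bias

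*Protocol article*

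**What the plan says.** Three places in the protocol article bear on this point.

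- **Statistical analysis.** The rule for continuous data is one sentence: "The continuous outcomes will be analyzed by t-test". Categorical primary and secondary outcomes go to the chi-square test and time-to-event outcomes to the log-rank test. The section then says that inference rests on the tests it has named, with confidence intervals when needed. No baseline-adjusted model is mentioned.
- **Secondary outcomes.** The functional outcome is "neurological functional status of 6 months after surgery measured by GOS", mRS, BI and NIHSS, each taken separately. The time point is 6 months.
- **Data collection and follow-up, with Table 1.** NIHSS is scheduled at baseline, 7 days, 1, 3 and 6 months. GOS, mRS and BI are scheduled at 1, 3 and 6 months, so BI has no baseline value.

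The one baseline score with a stated part in the group comparisons is GCS, which defines a subgroup. Baseline NIHSS has none.

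**The concern.** Enrolment spans GCS 5 to 12, so patients will differ in initial deficit. Allocation is by simple randomisation, so nothing in the design balances severity between arms. A t-test on raw 6-month NIHSS leaves in the error term whatever part of the 6-month spread baseline NIHSS could explain. A subgroup analysis by GCS does not remove it from the main comparison.

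What is at stake is the sensitivity of the NIHSS comparison, and of the BI comparison if BI is treated as continuous. The plan schedules the covariate that would sharpen both and then fixes a test that cannot use it. The primary outcome and the sample size are not touched.

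**Working it through.** **The plan's own figure.** The only sample size in the article is for the primary outcome: 2203 patients, for 58% against 51% poor outcome, two-sided 5% and 80% power. It reproduces exactly as an overall three-group chi-square test on 2 degrees of freedom with rates 0.58, 0.51 and 0.51:

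- mean rate = (0.58 + 0.51 + 0.51)/3 = 0.5333
- sum of squared deviations = 0.04667² + 2 × 0.02333² = 0.003267
- non-centrality = (2203/3) × 0.003267/(0.5333 × 0.4667) = 9.64, which gives power 0.800

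This figure does not depend on how NIHSS is analysed. The article states no power, standard deviation or correlation for NIHSS or any other continuous outcome, so the rest is conditional.

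**Inputs.** From the article: 816 patients per arm, two-sided 5%. Assumed: a correlation ρ of 0.3 to 0.6 between baseline and 6-month NIHSS, and 80% power for the unadjusted comparison as a reference point.

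**Formulas, for one pair of arms.**

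- Variance after linear baseline adjustment, relative to the t-test: 1 − ρ²
- Equivalent number per arm: 816/(1 − ρ²)
- Detectable difference in SD units at 80% power: (1.960 + 0.8416) × √(2(1 − ρ²)/816)
- Power at the difference the t-test detects with 80%: Φ(2.8016/√(1 − ρ²) − 1.960)

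| ρ (assumed) | Variance factor | Equivalent n per arm | Detectable difference (SD) | Power |
|---|---|---|---|---|
| t-test, unadjusted | 1.00 | 816 | 0.139 | 80% |
| 0.3 | 0.91 | 897 | 0.132 | 84% |
| 0.4 | 0.84 | 971 | 0.127 | 86% |
| 0.5 | 0.75 | 1088 | 0.120 | 90% |
| 0.6 | 0.64 | 1275 | 0.111 | 94% |

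The variance falls by 9% to 36%. That is worth 1/0.91 = 1.10 to 1/0.64 = 1.56 times the patients.

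**If only survivors are scored.** The Background gives a 30-day case fatality of 30% to 55%. If that held in this trial, 816 × 0.70 = 571 to 816 × 0.45 = 367 patients per arm would have a score. The t-test would then detect 0.166 to 0.207 SD. With adjustment (multiply by √0.91 = 0.954 or √0.64 = 0.80) this becomes 0.158 to 0.197 SD at ρ = 0.3, or 0.133 to 0.165 SD at ρ = 0.6. The correlation among survivors is also unknown.

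**If deaths are ranked worst.** A large share of patients would then be tied at one level. The factor 1 − ρ² belongs to a linear model on a continuous score and does not carry over directly. The gain may be smaller.

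**The case against.** The strongest defence is that nothing here is invalid. The secondary outcome is defined at 6 months and a 6-month comparison matches it. Under randomisation, an unadjusted comparison of all randomised patients is unbiased and keeps its 5% level. Chance imbalance in baseline NIHSS is already part of the t-test's standard error, so it is not a second harm. With 816 per arm it lies within 1.96 × √(2/816) = 0.10 SD in 95% of trials. All of this stands.

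The second defence is that covariate adjustment of secondary outcomes is commonly left to an SAP, and none is shown. This stands only in part. The article is not silent: it names the t-test and bases inference on the tests it lists. An SAP with an adjusted model would depart from the published text.

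The third defence is that the size rests on an assumed correlation and an assumed 80% starting power. That is correct, and the figures should be read as a range.

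A reader might infer three stronger points that the article does not support.

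- *That a longitudinal analysis was promised.* The Discussion says: "The complications and trends towards improved neurological outcome will also be investigated in this study". This is a single undefined phrase, it can simply mean a tendency to better outcome, and the Study objective section lists no trajectory. It gives no basis for requiring arm-by-visit models.
- *That the baseline and interim scores go unused.* The plan also says: "The descriptive analysis of all measurement data is implemented using mean, standard deviation, median, interquartile range, maximum and minimum indicators". That covers every visit. What baseline NIHSS lacks is a role in inference.
- *That all functional scales are tested by t-test.* GOS and mRS are category scales and can go to the chi-square test. The t-test reaches NIHSS and perhaps BI.

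**Conclusion.** The point holds as one of efficiency in a secondary outcome. The article fixes an unadjusted t-test for 6-month NIHSS, and for BI if continuous, although baseline NIHSS is scheduled and has no inferential role. For an assumed correlation of 0.3 to 0.6, the plan forgoes a 9% to 36% cut in the variance of the contrast, or a rise in power from 80% to about 84% to 94%. This assumes a linear model on scored patients. The corresponding figure for BI depends on its correlation with baseline NIHSS, which is also not given. There is no bias and no inflation of the error rate from this choice, and the primary analysis is unaffected. The change is worth making because it is specific and uses data already scheduled.

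**What to change.** In the Statistical analysis section:

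1. Replace the t-test for 6-month NIHSS with a linear model on treatment arm as a three-level factor, adjusted for baseline NIHSS.
2. Analyse 6-month BI, if treated as continuous, in the same way with baseline NIHSS as covariate, since BI has no baseline value.
3. If deaths are ranked as the worst outcome, use a rank-based or ordinal version of the same model, and say which.
4. Keep 6 months as the time point. No longitudinal model is needed for this purpose.

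The cost is a change of wording, made before any comparison by arm is seen. Table 1 already schedules the data and the plan already names SAS or SPSS, so no visit, measurement or patient is added.

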### Outcomes

#### Primary outcome

The primary outcome of this study is the unfavorable outcome at 6 months. The unfavorable outcome includes death and dependency after randomization. The dependency will be defined by using the Glasgow Outcome Scales (GOS) at 6 months after randomization.

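### A t-test on the 6-month Barthel Index and NIHSS, which appear to fall under the continuous outcomes, would compare survivors only or depend on the score given to the dead

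*Protocol article*

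**What the plan says.** The Secondary outcomes section lists neurological function at 6 months, "measured by GOS, Modified Rankin Scale (mRS), Barthe index (BI), and National Institutes of Health Stroke Scale (NIHSS) separately". The Statistical analysis section provides three tests: chi-square for categorical outcomes, log-rank for time-to-event outcomes, and for the rest, "The continuous outcomes will be analyzed by t-test". The same section commits to intention to treat: "The “intension to treat” analysis will be applied in this study".

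The article gives no cut-point that would make BI or NIHSS categorical, and neither is a time to an event. The t-test is therefore their natural place. This is an inference, because the sentence names no outcome.

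On deaths, the Background section reports for the disease in general: "The case fatality rate of sICH at 30 days is about 30%-55"%. The article states no expected mortality for the trial's own population. Death is handled explicitly elsewhere. For the primary outcome, "The unfavorable outcome includes death and dependency after randomization", and a separate secondary outcome is "mortality at 30 days, and 6 months after surgery".

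**The concern.** A patient who has died has no BI or NIHSS. GOS and mRS have a level for death; these two scales do not. A comparison of means can then be run in two ways.

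- **Available scores only.** The groups compared are the survivors of each arm. Survival happens after randomization and may be changed by the surgery, so this is not the intention-to-treat comparison that the section promises. An arm that keeps very sick patients alive adds low-functioning survivors to its mean and can look worse, although no patient did worse. An arm that loses its sickest patients can look better.
- **A number for the dead.** All randomized patients are kept, but the size of the mean difference, and so its significance, depends on the number assigned.

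The Study objective section sets out to evaluate effects on death and on dependency through physical function, and these scales contribute to that. A significant p-value pointing the wrong way would be awkward to explain in the report.

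**Working it through.** The protocol gives no figure for the BI or NIHSS comparison, so there is none to reproduce. The only design input used is the arm size, 816. For the record, the stated 2203 is reproduced by a three-group, 2-df chi-square at 58%/51%/51% (noncentrality 9.635, N = 2202.2), and 2203/0.90 gives 2448 = 3 × 816. The point here does not depend on it.

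**Set-up.** Two arms of 816. A is the proportion who would survive on either arm, and S is the extra proportion saved in the better arm. Nobody else changes. All means, SDs, scale limits and arm-specific mortalities below are assumptions.

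**1. Survivors only.** The expected difference is S/(A+S) × (mean of saved − mean of other survivors).

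Hand check for BI, without clipping to the scale: mortality 35% versus 30%, other survivors mean 65 (SD 30), saved mean 15.
- Difference = 0.05/0.70 × (15 − 65) = −3.57.
- Survivors: 816 × 0.65 = 530.4 and 816 × 0.70 = 571.2.
- Control variance 900. With SD 15 in saved patients, the better-arm variance is 0.9286 × 900 + 0.0714 × 225 + 0.0714 × 0.9286 × 50² ≈ 1018.
- SE = √(900/530.4 + 1018/571.2) ≈ 1.87, so z ≈ −1.91. Significant harm appears in about half of trials.

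Simulated results (2,000 trials each), other survivors mean 60, SD 30; saved patients SD 20; scores clipped to 0–100:

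| Mortality | Saved patients' mean BI (before clipping) | Survivor difference | Significant harm |
|---|---|---|---|
| 30% v 25% | 15 | −2.8 | 40% |
| 30% v 23% | 15 | −3.7 | 64% |
| 55% v 48% | 15 | −5.5 | 78% |
| 30% v 25% | 30 | −1.9 | 21% |
| 30% v 23% | 30 | −2.6 | 38% |
| 55% v 48% | 30 | −3.8 | 48% |
| 30% v 23% | 60, SD 30 (same as others) | 0.0 | 2.6% |
| 30% v 30% | none saved | 0.0 | 3.0% |

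With other survivors at mean 65 and saved patients at about 15, a second simulation gives harm in 50–52% (35% v 30%), 78–79% (35% v 28%) and 84% (7 points saved from 45%).

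NIHSS, normal approximation, 30% v 23%, assumed means 10 and 22, SD 7: difference = 0.07/0.77 × 12 = +1.09 (worse), significant harm in 72%.

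**2. Deaths given a score v.** Everyone is kept, and the expected difference becomes S × (mean of saved − v).
- BI, v = 0, saved mean 15 before clipping: simulated differences of +0.8 (30% v 25%) to +1.3 (30% v 23%), benefit in 6% to 11%, harm below 1%.
- NIHSS, 30% v 23%:
  - v = 25: 0.07 × (22 − 25) = −0.21, significant benefit in 7%.
  - v = 35: 0.07 × (22 − 35) = −0.91, significant benefit in 31%.
  - v = 42: 0.07 × (22 − 42) = −1.40, significant benefit in 46%.

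The data are the same in all three NIHSS cases; only the score assigned to death differs.

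**3. Rank test with death worst.** In the 35% mortality scenarios for BI, harm was declared in 0.1–0.6% of trials, and benefit in 12–13% (5 points saved) and 18–19% (7 points saved).

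**The case against.** - **The routing is inferred.** The only plainly continuous secondary outcome is days of hospitalization, and the scales could be dichotomised in an analysis plan not shown. This stands as a limit on certainty. It does not remove the point: no cut-point is given, and of the three tests offered the t-test fits best. A missing rule for deaths would not be a finding by itself. The point is that a comparison of means is stated for what appear to be scores undefined after death.
- **A reader might infer that no t-test could be valid here.** The calculations do not support that. Scoring deaths at the worst value preserves the randomized comparison, and for BI harm stays below 1%. What remains is dependence on the score, shown for NIHSS in the chance of benefit and not as harm. Ranking death last is also a value choice, but it needs no distance between death and the worst survivor.
- **A reader might infer that a third to a half of patients will have no score.** The 30% to 55% is background 30-day fatality for the disease in general, not a plan assumption for operated patients aged 15 to 75 without terminal herniation. At 55% dead, only 58 − 55 = 3 points would be left for dependency within the assumed 58%.
- **The harm scenario is not the plan's hypothesis.** Patients saved into severe disability leave the unfavorable-outcome rate unchanged, whereas the Sample size section assumes a fall from 58% to 51%. Take mean BI 85 if favorable and 30 if dependent (assumed). Control with 35% dead, 23% dependent and 42% favorable gives (23 × 30 + 42 × 85)/65 = 65.5. The better arm with 30% dead and 51% unfavorable gives (21 × 30 + 49 × 85)/70 = 68.5; with 28% dead, (23 × 30 + 49 × 85)/72 = 67.4. Survivor means rise, so there is no reversal. This stands: the harm signal is possible, not expected.
- **Other outcomes guard against misreading.** The primary outcome, mortality, GOS and mRS all register death and would be reported alongside. This limits the damage but does not correct the BI or NIHSS p-value.

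**Conclusion.** The concern holds for two secondary scales. If the 6-month BI and NIHSS go to a t-test on available scores, the comparison is among survivors and departs from intention to treat. Where a technique saves 5 to 7 percentage points of patients who function worse than other survivors, the test declares significant harm in roughly 20% to 80% of trials. The result is most sensitive to the function of the saved patients: the bias vanishes when they resemble other survivors or when mortality is equal. If deaths are scored instead, harm does not appear in the cases examined, but the NIHSS result moves with the chosen score (benefit in 7% to 46%).

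These sizes rest on assumed means, SDs and mortalities, and on the inference that the t-test sentence covers the two scales. A reader might take this to undermine the trial's main conclusion. It does not: the primary outcome counts death, and mortality, GOS and mRS are unaffected.

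**What to change.** In the Statistical analysis section, name the 6-month BI and NIHSS. State that each is analysed in all randomized patients by a rank-based method (Wilcoxon or Kruskal-Wallis) or a proportional-odds model, with death ranked below the worst survivor score. State also that survivor means are descriptive only and labelled as conditional on survival.

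This changes analysis wording only and needs no new data, visits or patients. The cost is that the effect is a rank or odds measure and not a difference in scale points, which clinicians may find harder to read. Because it combines death with function, it should be read beside the separate mortality results.
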